	5. LVEF >20%
	6. ICD implant
	7. Signed informed consent
	8. Life expectation >1 year in absence of VT
Exclusion criteria	9. ICD interrogation demonstrating polymorphic VT
	10. Patients with INTERMACS class >4
	11. Patients with LVADs
	12. Patients with ongoing neoplastic disease
	13. Previous thoracic RT with cardiac involvement
	14. Active myocardial ischemia
	15. Cardiac revascularization <120 days

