## Populations

Our aim is to enroll patients with structural heart disease, in whom the presence of a myocardial scar induces refractory monomorphic VT or ventricular fibrillation (VF), as documented by either implantable cardioverter defibrillator (ICD) appropriate shocks or anti-tachycardia pacing (ATP) at ICD interrogation. We will enroll patients with recurrent VT/VF episodes despite optimal medical therapy (i.e., class III antiarrhythmic drugs) and at least one previous attempt of RFA or patients in whom ablation is not feasible, because of contraindications to the procedure or of patient intolerance. Previous percutaneous stellate ganglion blockade is neither a requirement for inclusion criteria nor exclusive criteria that will be collected in the standardized data collection for potential subgroup analysis.

Eligibility criteria are summarized in Table 1.

**TABLE 1 T1:** Inclusion and exclusion criteria.

Inclusion criteria	1. Patients with structural heart disease and monomorphic VT refractory to optimal medical therapy and previous RFA attempts (minimum of one attempt RFA)
	2. Patients with contraindications to conventional ablation or not suitable for any non-interventional approach, refusing any surgical ablative attempt; or patients who have already undergone RFA with arrhythmogenic focus refractory to previous ablation procedures
	3. Age >18 years
	4. Candidates not suitable for heart transplantation

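### On the scale's usual numbering, the INTERMACS exclusion in Table 1 runs opposite to the other severity criteria and can be read two ways across centres

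*Protocol article*

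**What the plan says.** The eligibility criteria are in Table 1 of the protocol article, under Populations. Exclusion item 10 reads "Patients with INTERMACS class >4". INTERMACS is mentioned nowhere else in the article, and no range, direction or description of the classes is given.

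Three other items in the same table limit how sick a patient may be. Inclusion item 5 requires an LVEF above 20%. Inclusion item 8 requires "Life expectation >1 year in absence of VT". Exclusion item 16 bars NYHA IV.

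Two further items concern advanced heart failure without grading it: inclusion item 4 ("Candidates not suitable for heart transplantation") and exclusion item 11 ("Patients with LVADs").

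Table 2, under Methods/design, stars NYHA group and LVEF as mandatory matching factors. INTERMACS class is not a matching factor there or in the list in the statistical section. The primary outcome, under Outcome measures, is overall cardiovascular survival. Data in both groups may be collected prospectively or retrospectively (Protocol overview).

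**The concern.** An eligibility list should grade severity in one direction. Items 5, 8 and 16 each remove patients at the sick end. If INTERMACS is numbered in its usual way, from 1 (most severe) to 7 (mildest), the inequality in item 10 removes patients at the milder end. That is the pattern one would see if the cut-off had been written as though INTERMACS ran in the same direction as NYHA, although the article does not show how it arose.

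What is at stake is the population to which the result applies, and whether centres enrol the same one. Recruitment is multicentre, and investigators apply the list to their own prospective cases and retrospective series. Heart failure severity is a plausible driver of cardiovascular survival, so two readings of one severity item could give different case mixes by centre.

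**Working it through.** No figure in the plan depends on this item, so there is nothing to recompute. The check sets the criteria side by side and applies them jointly: a patient must meet every inclusion and no exclusion.

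**Inputs from Table 1:** items 5, 8, 10, 11 and 16, as described above.

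**Assumptions, not in the article:** (a) INTERMACS profiles run from 1, the most severe (cardiogenic shock), to 7, the mildest (advanced NYHA III); (b) patients in profiles 1 to 4 generally have NYHA IV-level symptoms. These are the standard meaning of a named clinical scale. Taking NYHA IV to be the worst NYHA class needs knowledge of the same kind.

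**Step 1: item 10 alone, read literally.** Classes above 4 are 5, 6 and 7, so 7 − 4 = 3 profiles are excluded, and they are the milder ones. Profiles 1 to 4 pass this item. Items 5, 8 and 16 point the other way.

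**Step 2: all items together, read literally.**

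| Patient | Item 10 | Item 16 (NYHA IV) | Items 5, 8, 11 | Net |
|---|---|---|---|---|
| Profiles 1 to 4 | not excluded | mostly excluded | may exclude some | mostly excluded |
| Profiles 5 and 6 | excluded | not needed | not needed | excluded |
| Profile 7 (advanced NYHA III) | excluded | not excluded | do not necessarily exclude | excluded by item 10 only, if the rest are met |
| Not on the INTERMACS scale | not excluded | depends on NYHA class | depends on patient | eligible if the rest are met |

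So the joint list does not admit the sickest. It removes nearly every patient who can be placed on the scale at all.

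**Step 3: item 10 read as too sick.** Under this reading item 10 agrees in direction with item 16, and a profile 7 patient is not stopped by it.

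**Step 4: compare the readings for one patient.** Take a patient in NYHA III, profile 7, with LVEF above 20%, life expectation above one year and no LVAD, who meets all the other items. A literal centre turns this patient away; a centre reading the item as too sick enrols the patient. Item 16 bars only class IV, so nothing else in the severity items decides the case. NYHA group is also a mandatory matching factor, so the plan expects more than one NYHA class among enrolled patients.

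**Step 5: does another item settle the direction?** Items 4 and 11 concern transplant suitability and an implanted device. Neither says which end of the INTERMACS scale is worse.

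**The case against.** The strongest reply is that the article never states the direction of the scale. If a higher class meant a sicker patient, item 10 would agree with item 16 and there would be no issue. That is correct, and it is why the direction is declared here as an assumption. It does not dispose of the point: the item names an established scale, and a centre applying it will use that scale's own numbering.

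A second reply is that an article condenses the full protocol, which may define the classes. That also stands, so the absence of a definition is not the complaint. The complaint is the direction of a cut-off that Table 1 does state.

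A third reply is that matching protects the comparison. In large part it does. NYHA group and LVEF are mandatory factors and stay in force if enrolment falls back to mandatory factors only. The same list also governs both groups. No residual imbalance between groups has been shown, and none is claimed. Matching acts on patients already judged eligible, however, so it cannot settle who enters.

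Two stronger readings are tempting. A reader might infer that the plan keeps the sickest patients. The document does not support this, because item 16, with items 5, 8 and 11, removes most of profiles 1 to 4. A reader might also infer that the criteria contradict one another. They do not in the strict sense: exclusions add up, and no item requires a patient whom another forbids. The fault is one of direction.

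**Conclusion.** The point holds as an inconsistency of direction in a stated eligibility rule, conditional on the usual INTERMACS numbering. Read literally, item 10 excludes 3 of 7 profiles, the milder ones, and runs opposite to items 5, 8 and 16. The identified loss that no other severity item would necessarily cause is NYHA III patients in profile 7. The article gives no INTERMACS distribution, so neither the share of candidates affected nor any shift in the survival comparison can be put in numbers. Divergent application across centres is a foreseeable risk, not something the article demonstrates.

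The sample size of 149 (100 controls and 49 VT-ART patients) is untouched. The item should be corrected because it helps define the study population and the correction is cheap. It does not undermine the design.

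**What to change.** Reconcile item 10 with items 5, 8 and 16. Replace the inequality with an explicit list of the excluded INTERMACS profiles, each given by number and description, so that the item no longer depends on the reader's view of which end is worse. Apply the same list to prospective and retrospective patients in both groups. Which profiles to exclude is a clinical decision for the sponsor, and no cut-off is proposed here.

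The cost is a one-line amendment to Table 1 and a matching change to the eligibility check in the electronic case report form. No extra patients or procedures are needed. If patients have already been enrolled, their eligibility should be rechecked against the clarified list.

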	16. NYHA IV
	17. Pregnant women

## Methods/design

Our trial will investigate the effects of administering a single fraction of external beam radiation delivered through SBRT techniques at a dose of 25 Gy on patients with recurrent episodes of VT and in whom optimal medical therapy and previous RFA attempts have failed to provide benefit from VT burden control. We will perform matched pair analysis with dynamic cohorts. We will compare two groups of patients: One that has been treated by all the standard approaches but has not undergone VT-ART and a second group that has also received VT-ART. The entire enrolled group (by multicentric recruitment) will be stratified according to some predefined characteristics and analyzed by matched pair analysis, based on the characteristics of patients treated with VT-ART. Once a patient is enrolled to undergo VT-ART within the multicentric consortium, the search for two patients with similar feature profiles not undergoing VT-ART will be shared.

Matching factors taken into account are summarized in Table 2.

**TABLE 2 T2:** Applied matching factors.

Parameter type	Subgroup options
Etiology of cardiomyopathy*	ICM
	NICM
	ACM
Age*	
Gender*	
BMI	
LVEF*	
NYHA group*	
Ventricular arrhythmia presentations*	Sustained ventricular tachycardia incessant sustained ventricular tachycardia electrical storm
Arrhythmogenic focus anatomical intracardiac location	Based on VE exit by ECG and by the activation map of VT
Diagnostic tools used for scar definition	CT
	MR
	EAM
	ECG
TA volume*	Endocardial electroanatomic substrate mapping area/volume in all cases; epicardial mapping area/volume in the case of 3D epicardial electroanatomic substrate mapping
Heart volume	cc range
Heart-to-TA volume	cc range
Previous use of amiodaron	Y/N
Number of previous RFA attempts*	
Type of previous RFA attempts	endocardial
	epicardial
Unfeasibility to repeat RFA	Y/N
Local recurrence of TA (same area of last RFA)	Y/N
Previous percutaneous stellate ganglion blockade	Y/N

TA, target area by electroanatomical mapping; BMI, body mass index; RFA, radiofrequency ablation; LVEF, left ventricle ejecting fraction; *mandatory matching factor.

Figure 1 depicts the design of the VT-ART study.

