Other secondary objectives include identifying the benefits of VT-ART on cardiac function, as evaluated through an electrocardiogram, echocardiographic, biochemical variables, and patient’s quality of life.

In particular, we will evaluate the reduction or suspension of antiarrhythmic drug use compared to the baseline and the improvement of cardiac parameters (such as LVEF, left ventricular end-diastolic volume/diameter, ventricular strain, end-systolic volume/diameter, RVEF, and TAPSE for right ventricular function).

Analyzed biochemical variables will include heart failure biomarkers, such as NT-proB-type natriuretic peptide (NTproBNP), troponin (hs-TnI), and inflammation markers, such as polymerase chain reaction (PCR), tumor necrosis factor-alpha (TNF-alpha), and interleukin 6 (IL-6).

Improvement in the patient’s quality of life will be assessed compared to the pre-treatment period using the SF36 scale.

The patient’s QoL will be assessed before and after VT-ART using the SF36 scale (6); the post-treatment score will be compared to the pre-treatment period’s one to assess potential improvement. The post-treatment QoL evaluation will be performed at 3, 6, and 12 months after VT-ART. Once centers join the consortium, the SF36 QoL scale will be offered (although not mandatory) to all patients undergoing RFA: Before and at 6 months after conventional therapy.

Secondary outcome analyses will investigate the improvement of QoL scores after VT-ART and how QoL scores change the comparison between VT-ART and RFA.

Further secondary outcome analyses will be developed through imaging: Contrast infusion MRI and CT scan will be performed as required but not mandatory (if not contraindicated due to ICD) in the experimental arm.

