### Statistical considerations and sample size for matched pair analysis

A descriptive analysis will summarize the total number and stratification of patients with RFA and VT-ART.

We will perform a comparative analysis between RFA and VT-ART in patients with structural heart disease and refractory VT. Each patient who will be treated by VT-ART will be compared with two patients in the control group treated with RFA and best standard care but without VT-ART, on the basis of the following matching factors: Etiology of cardiomiopathy (ICM, NICM, and ACM), ventricular arrhythmia presentations (sustained ventricular tachycardia; incessant sustained ventricular tachycardia; and electrical storm), diagnostic tools used for scar definition (CT, MR, EAM, and ECG), arrhythmogenic focus anatomical intracardiac location (on the basis of VE exit by ECG and by activation map of VT), TA volume (endocardial electroanatomic substrate mapping area/volume in all cases; and epicardial mapping area/volume in case of 3D epicardial electroanatomic substrate mapping), heart volume, heart-to-TA volume, rate number of previous RFA attempts, type of previous RFA attempts (endocardial and epicardial), time (in days) between the first RFA attempt and VT-ART, time (in days) between the last RFA attempt and VT-ART, previous percutaneous stellate ganglion blockade, time (in days) between the percutaneous stellate ganglion blockade and VT-ART previous use of amiodaron, NYHA group, LVEF, BMI, age, and gender.

As mentioned, applied matching factors are summarized in Table 2.

Continuous data will be expressed as mean ± standard deviation, as appropriate, for all variables collected from the entire population or specific subgroups. A comparative analysis for subsequent levels of qualitative variables through the chi-square test and quantitative variables (scores on quality of life) with the *T*-test will be performed.

Non-parametric tests will be provided where the population distribution does not have a known form (normal Gaussian).

The differences in baseline and follow-ups between the same group will be analyzed with repeated measures approach: using the Friedman test and MANOVA for continuous variables and McNemar or Cochran’s *Q*-tests for categorical ones.

The significance of the tests is fixed with *p* < 0.05.

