Once the planned number of the innovative procedure will be collected, the trial will put a 6-month observation time. If after that, 60% of the planned conventional arm patients will be collected (by all matching factors and in a 2:1 ratio), a further 3 months will be provided to reach the planned accrual. If that would have not been the case, then the patient’s enrollment will be allowed by mandatory matching factors only (only beyond that point). The detail of “mandatory matching factors” is reported in Table 2. The final analysis will be performed by the whole group and subgroup analyses, discriminating patients collected through “all matching factors” and by “mandatory-only.”

The final analysis will not be performed at all if less than a 1:1 ratio (conventional: Innovative group) of patient’s enrollment will be collected, and the study will be closed.

The final analysis will be performed specifying that the planned accrual is not met if at least a 1:1 ratio (conventional: Innovative group) enrollment will be accomplished; results will be explored and cautiously evaluated.

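### The only drug-related matching factor is past amiodarone use, which is optional and does not describe antiarrhythmic treatment at the index procedure, so drug differences could be read as a VT-ART effect on the arrhythmia endpoints

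*Protocol article*

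**What the plan says.** **Matching factors.** Table 2 (Methods/design) has one drug item, "Previous use of amiodaron", answered Y/N. It carries no asterisk, and the table footnote defines the asterisk as "mandatory matching factor". The longer list under Statistical considerations again has only this drug item: "previous use of amiodaron, NYHA group, LVEF, BMI, age, and gender". Neither list contains the drugs taken at the index procedure or how many there are.

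**Fallback.** If too few controls have been found 6 months after VT-ART accrual is complete, Sample size says "then the patient’s enrollment will be allowed by mandatory matching factors only (only beyond that point".

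**Background treatment.** Populations requires "recurrent VT/VF episodes despite optimal medical therapy (i.e., class III antiarrhythmic drugs". The comparison group is described as "two patients in the control group treated with RFA and best standard care but without VT-ART", with no drugs specified. Retrospective controls may be up to 5 years older than the matched VT-ART enrolment (Sample size).

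**Analysis and outcomes.** The comparative tests named are "qualitative variables through the chi-square test and quantitative variables (scores on quality of life) with the" t-test, plus non-parametric and repeated-measures tests. Under Outcome measures, drug use is itself an outcome: "we will evaluate the reduction or suspension of antiarrhythmic drug use compared to the baseline".

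**The concern.** The groups are not randomised, so comparability rests on the matching list and on whatever adjustment the analysis adds. Ventricular event-free survival and VT burden are read from the ICD, and antiarrhythmic drugs act directly on what the ICD records. What matters for those endpoints is the regimen at time zero. A Y/N answer on past amiodarone treats a patient still taking it and a patient who stopped it as the same.

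If the groups start on different regimens, part of any difference in the arrhythmia endpoints is a drug effect. It could inflate or mask a VT-ART effect. The drug-reduction objective has a related difficulty: a patient already off a drug at baseline cannot reduce or stop it, so the baseline mix partly determines the result.

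**Working it through.** **Step 1: what remains under each matching rule.**

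- All factors: one drug item, past amiodarone Y/N.
- Mandatory factors only: etiology, age, gender, LVEF, NYHA group, arrhythmia presentation, TA volume and number of previous RFA attempts. No drug item remains.
- Regimen at the index procedure: absent under both rules.

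**Step 2: inputs.**

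- Group sizes 49 and 100, and a target difference of 20 percentage points in VT-burden control (Sample size; the stated 20% is read as points).
- Significance level 0.05 (Statistical considerations); two-sided is my assumption.
- Control rate: none is stated. I use 50–75%, the complement of the 25–50% recurrence after RFA cited in the Discussion. That figure is not specific to this refractory population.
- Drug imbalance of 30 points and drug effect of 10–25 points on the control rate. Both are assumptions; the article gives neither.

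The planned total of 149 cannot be reproduced from the stated inputs, because the control rate is missing. A two-sided, uncorrected calculation with 10% dropout gives 147 for 10% versus 30%, and 150 for 72% versus 92%. Nothing below depends on this.

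**Step 3: bias.** Spurious difference = imbalance × drug effect.

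- Low end: 0.30 × 0.10 = 0.030, or 3.0 points (15% of the 20-point target).
- High end: 0.30 × 0.25 = 0.075, or 7.5 points (37.5% of the target).

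**Step 4: false-positive rate with no true VT-ART effect.** Let pC be the control rate, pT = pC + bias, and p̄ = (49·pT + 100·pC)/149. Then s0 = √[p̄(1−p̄)(1/49 + 1/100)] and s1 = √[pT(1−pT)/49 + pC(1−pC)/100]. The rejection probability is 1 − Φ[(1.96·s0 − bias)/s1] + Φ[(−1.96·s0 − bias)/s1].

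Example with pC = 0.50 and bias 0.075: p̄ = 0.5247, s0 = 0.0871, s1 = 0.0865. The upper tail is 0.134 and the lower tail 0.002, so the total is 13.7%.

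| Control rate | Bias 3.0 points | Bias 7.5 points |
|---|---|---|
| 50% | 6.3% | 13.7% |
| 62.5% | 6.3% | 14.1% |
| 75% | 6.5% | 16.5% |

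Other assumed inputs, at control rates of 30–50%: 20 × 20 points gives a 4-point bias and 7–8%; 40 × 30 points gives a 12-point bias and 28–31%. None of these scenarios creates the full 20 points.

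**Step 5: bias in the other direction.** With a true 20-point effect and a 7.5-point bias against VT-ART, power depends on which rate is moved.

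| Control rate | No bias | Control rate raised | VT-ART rate lowered |
|---|---|---|---|
| 50% | 64.5% | 30.8% | 29.8% |
| 75% | 89.7% | 57.0% | 41.4% |

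**The case against.** **Eligibility already standardises treatment.** Every patient must have recurred despite class III therapy, and controls receive best standard care. This stands in part: it narrows the differences. It does not fix which drugs, or how many, a patient takes at time zero.

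**VT burden is a before-and-after measure.** A drug effect that is the same in both windows would partly cancel. This also stands in part. It does not help if the regimen changes around the procedure, and event-free survival has no pre-procedure window.

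**Adjustment may be specified elsewhere.** This is a condensed article, and covariate lists usually belong in the SAP. A reader might infer that the trial will not adjust for drugs at all. The article does not support that; it shows only that none of the tests it names is a covariate model. The matching list is different: it is given twice, with its mandatory items marked, so it is a choice already made.

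**The matching factor is nearly constant.** A reader might also infer that eligibility makes almost everyone a past amiodarone user, so that the factor separates nobody. Populations names class III drugs, not amiodarone, and no exposure rate is given. The point does not need this step, because past use fails to describe current treatment even if it varies.

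**The endpoints are secondary and the size is assumed.** Both are true. The primary endpoint is cardiovascular survival, and no effect on it is argued here. At the low end the false-positive rate is close to nominal. Nothing in the text says which group would be favoured.

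**Conclusion.** The point holds as a gap in the published matching design. The one drug factor describes past exposure, is optional, and disappears for controls enrolled under the fallback. Eligibility controls background treatment only partly, and controls may be several years older, so a difference in regimen at the index procedure can be mistaken for a VT-ART effect, or hide one, on VT burden and ventricular event-free survival.

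Under the stated assumptions the bias is 3.0–7.5 points of a 20-point target, with a false-positive rate from about 6% to 14–17%. These are illustrations: the imbalance, the drug effect and the control rate are all assumed, and the direction is unknown. The affected endpoints are secondary, but VT-burden control is the quantity on which the sample size rests, so the improvement is worth making.

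**What to change.** - Record the antiarrhythmic regimen at the index procedure in both groups: current amiodarone Y/N and number of antiarrhythmic drugs.
- Pre-specify that regimen as an adjustment covariate in the VT-burden and ventricular event-free survival comparisons. Use the baseline value only; later drug changes follow the procedure and are an outcome in their own right.
- Evaluate drug reduction or suspension among patients on the drug at baseline.
- Keep past amiodarone use as a descriptive variable. If the SAP already contains such an adjustment, a cross-reference is enough.

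**Cost.** No extra patients and no change to treatment. The baseline regimen is already needed for the drug-reduction objective in VT-ART patients. The article does not establish that it is collected for RFA controls, so for retrospective controls it must be abstracted from records. Some values may be missing, and the plan should say how those are handled.

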## Outcome measures

The primary outcome is investigating the difference in overall cardiovascular survival among the group undergoing VT-ART and the one not exposed to the innovative procedure.

The primary efficacy endpoint is a statistically significant difference in overall cardiovascular survival between the group undergoing VT-ART and the one not exposed to the innovative procedure; this will be defined in months and calculated from the time of the last procedure (represented by the last RFA for the control group and VT-ART for the innovative one, respectively).

The secondary outcome is evaluating the difference in ventricular event-free (referred to VT/VF, appropriate shock or ATP as recorded by the ICD) survival after the last procedure between the two groups (i.e., the single or last RFA in the control group and VT-ART in the innovative group). The respective endpoint is a statistically significant difference in ventricular event-free survival (in months) after the last procedure between the two groups.

An additional secondary aim is to evaluate the reduction in the number of VT episodes compared to the pre-treatment period between the two dynamic cohorts that will be investigated.

Ventricular tachycardia recurrence will be defined as evidence of monomorphic VT at ICD interrogation (either self-limiting or terminated by appropriate shock therapy or ATP). The number of VT episodes, defined as VT burden, in the 3 months before and after the procedure will then be compared.

The respective secondary endpoint will be evaluated facing 3 months before the last procedure (i.e., either RFA or VT-ART) and 3 months after.

We did set a blanking period after VT-ART before evaluate the effect on VT burden; in a recent study by Kautzner et al., the authors supported the pre-clinical theorem of myocardial apoptosis (up to 3 months post-stereotactic ablation) followed by a creation of fibrotic lesion (6–9 months post-stereotactic ablation) in the irradiated region (5). Consequently, we propose a 3-month-blanking period after the procedure.

Since a blanking period of 3 months after the procedure will be applied, the secondary endpoint will evaluate the number of VT episodes interval accounted for the last 3 months before the procedure and of the 3–6 months after it.

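### Local recurrence after the last RFA is history in a VT-ART patient but, as written, a post-time-zero event in a control, so all-factors matching partly selects controls on a secondary endpoint

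*Protocol article*

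**What the plan says.** **Time zero.** Outcome measures counts the primary endpoint from the last procedure, "represented by the last RFA for the control group and VT-ART for the innovative one, respectively". For the secondary endpoint the index procedures are "the single or last RFA in the control group and VT-ART in the innovative group", so a control may have had only one RFA.

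**Endpoints.** "The primary efficacy endpoint is a statistically significant difference in overall cardiovascular survival". The first secondary endpoint is "a statistically significant difference in ventricular event-free survival (in months) after the last procedure between the two groups". The same section adds: "Ventricular tachycardia recurrence will be defined as evidence of monomorphic VT at ICD interrogation". VT burden, a further secondary endpoint, compares the 3 months before the procedure with months 3 to 6 after it, following a 3-month blanking period.

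**Matching.** Table 2 (Methods/design) includes "Local recurrence of TA (same area of last RFA", coded Y/N, and "Unfeasibility to repeat RFA", also Y/N. Neither carries the asterisk that marks a "mandatory matching factor". Controls are sought to fit the profile of each VT-ART patient, two per patient. The list of factors written out under Statistical considerations contains neither item, but that section refers the reader back to Table 2.

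**When the factors apply.** Under Sample size, all factors are used first. Mandatory-only matching opens only if the accrual check made 6 months after the VT-ART group is complete fails. The final analysis covers the whole group and, as subgroups, those matched on all factors and those matched on mandatory factors only. Retrospective controls are allowed.

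**The concern.** A matching factor should be known at or before time zero in both groups. Here the same words point to different sides of time zero. If a VT-ART patient is coded Y, the centre must look for controls in whom VT returned in the area of their last RFA. If that RFA is the control's index procedure, the centre is choosing controls because they had a ventricular recurrence during follow-up. A VT-ART patient coded N has the reverse effect: controls are chosen because they had no local recurrence during follow-up.

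To that extent the control event rate would reflect the history of the VT-ART group and not what RFA achieves. Retrospective controls make this workable in practice, because their course after the last RFA may already be known when they are selected. Selection of this kind cannot reliably be undone in the analysis.

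**Working it through.** **1. The factor against the clock**

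| Group | Time zero | Last RFA | Local recurrence after last RFA |
|---|---|---|---|
| VT-ART | VT-ART | before time zero | history, known at time zero |
| Control, single RFA | that RFA | is time zero | observable only after time zero |
| Control, two or more RFAs | the last RFA | is time zero, as written | after time zero, unless the RFA before the index one was meant |

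The second row admits no other reading, because no earlier RFA exists. In the third row a baseline reading is possible, but the article does not state it.

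**2. Is the matched event an endpoint event?** Event-free survival ends with VT/VF, appropriate shock or ATP recorded by the ICD, and recurrence is monomorphic VT at ICD interrogation. So a Y recurrence is of the kind that ends event-free survival, provided it falls in a period that the interrogations cover. For VT burden it counts only if it falls in months 3 to 6.

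**3. Direction.** Let y be the share of VT-ART patients coded Y. With two controls per patient, this is also the share of all-factors controls coded Y. Let L be the share of unselected controls with a local recurrence after the index RFA, and q the share of the remainder with some other ventricular event.

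- Unselected controls: R = L + (1 − L)q
- Matched controls: M = y + (1 − y)q
- Shift: M − R = (y − L)(1 − q)

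The shift favours VT-ART when y exceeds L and runs against it when y is below L. The article gives neither y, L nor q.

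**4. Illustration (y is assumed).** Discussion and final considerations cites 25–50% VT recurrence after RFA; take this as R. Since M is at least y, the shift is at least y − R.

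- y = 0.60: 0.60 − 0.50 = 0.10, to 0.60 − 0.25 = 0.35
- y = 0.90: 0.90 − 0.50 = 0.40, to 0.90 − 0.25 = 0.65
- y = 0.10, all recurrences local (q = 0, L = R): 0.10 − 0.25 = −0.15, to 0.10 − 0.50 = −0.40

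The sign changes over a range that the article does not rule out.

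**5. Effect on a test (also assumed).** Take 49 against 100 patients, no true difference, a two-sided 5% comparison of two proportions, true recurrence r, and a fraction f of controls coded Y, the others recurring at r. The control share is f + (1 − f)r.

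| r | f | Control share | Chance of falsely favouring VT-ART |
|---|---|---|---|
| 0.50 | 0.25 | 0.25 + 0.75 × 0.50 = 0.625 | 31% |
| 0.50 | 0.50 | 0.50 + 0.50 × 0.50 = 0.75 | 86% |
| 0.25 | 0.25 | 0.25 + 0.75 × 0.25 = 0.4375 | 61% |
| 0.25 | 0.50 | 0.50 + 0.50 × 0.25 = 0.625 | 99.5% |

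The nominal chance in that direction is 2.5%. The table leaves out the opposing pull of N matches. With r = 0.50, f = 0.25 and no event in any N-matched control, the control share would be 0.25, below 0.50, and the tilt would run against VT-ART. So the table shows only that the mechanism can matter at this sample size. It does not estimate the bias.

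**6. The plan's own figure.** The 149 patients cannot be uniquely reproduced, because no control rate is stated. One route that comes close is 10% against 30%, two-sided: 44 and 88, or 49 and 98 (147) after 10% drop-out. The present point does not depend on it.

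**The case against.** The strongest reply is that Table 2 is a baseline profile. The factor stands beside previous amiodarone use and the number of previous RFA attempts, the eligible population has already failed RFA or cannot have it, and RFA patients may also be enrolled prospectively. If such a patient is profiled before the index RFA, the last RFA can only be the earlier one, and the factor is sound. The full data-collection form, where timing may be defined, is not shown. This stands as a possible reading for controls with two or more RFAs. It does not help the single-RFA control, whom Outcome measures expressly admits, and nothing in the article states it.

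Several stronger readings are tempting, and the objection to each is right:

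- **The primary comparison is matched on its outcome.** It is not. The primary endpoint is cardiovascular survival; any effect on it is indirect.
- **The bias exceeds the difference the trial is sized for.** The 20% in Sample size concerns VT-burden response, and a recurrence at any time is a different quantity. The shares coded Y are assumed, and the cited 25–50% refers to structural heart disease generally, not to this refractory population.
- **Unfeasibility of repeat RFA has the same fault.** It is not a ventricular event, and the article links limited feasibility to anatomy and frailty, which can be known beforehand. It lacks a date, no more.
- **The fault is independent of the choice of time zero.** It is not. A control clock that starts after the failed RFA would make the factor baseline in both groups.
- **The all-factors set is the preferred analysis.** The article does not say so; it analyses the whole group and both subsets.

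**Conclusion.** The point holds in a limited form. As written, Table 2 and Outcome measures together make local recurrence a post-time-zero variable in controls, at least in every control with a single RFA. All-factors matching then partly selects controls on ventricular event-free survival, and to a lesser degree on VT burden. This is a stated rule with a faulty reference point, not merely a detail left to another document.

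Its reach is bounded. The factor is not mandatory, patients enrolled under the mandatory-only rule are not affected by it, the primary endpoint is not matched on directly, and the statistical section's list leaves the factor out. Direction and size depend on the unstated share of VT-ART patients coded Y. A high share is plausible, since Table 1 item 2 admits patients whose focus is refractory to previous ablation, and the tilt would then favour VT-ART. The article supports no numerical estimate.

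**What to change.** Before controls are matched:

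1. In Table 2, define every RFA-history factor as of the day before the index procedure in both groups. For a control, local recurrence then refers to the RFA before the index RFA.
2. Drop local recurrence from the matching where it cannot be defined in this way, as in single-RFA controls.
3. Date *Unfeasibility to repeat RFA* the same way, or drop it.
4. State that the index RFA is not counted in the number and type of previous RFA attempts.
5. Reconcile Table 2 with the list under Statistical considerations, which omits local recurrence and unfeasibility.

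The change is mainly one of wording in Table 2 and the matching form, but it has costs. The all-factors match has fewer usable factors. Some retrospective controls may lack the earlier mapping needed to place a recurrence after the RFA before the index one. Step 4 also touches *Number of previous RFA attempts*, which is mandatory, so the fallback match is affected to that extent.
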